### Aims and Hypotheses

The main aim of this study is (1) to investigate the feasibility of the Internet Attachment–Based Compassion Therapy (iABCT), a web-based version of ABCT, in the general population. Additional objectives are (2) to analyze the preliminary effects of iABCT on happiness, compassion, self-compassion, dispositional mindfulness, general health, purpose in life, nonattachment, attachment styles, self-criticism, and positive and negative affects at postintervention and 3-month follow-up; (3) to explore cost-effectiveness by means of changes in overall health status levels; (4) to investigate the mechanisms of change, predictors, and associations between outcomes; and (5) to assess adverse or unwanted effects and facilitators and barriers to the intervention received.

The principal hypothesis is that iABCT will be feasible and well accepted by participants in terms of attrition, expectations, satisfaction, usability, and opinion. Second, iABCT will show efficacy in promoting significant changes with moderate-to-large within-group effect sizes in self-reported measures of happiness, compassion, self-compassion, dispositional mindfulness, self-criticizing, nonattachment, purpose in life, attachment, and overall health status. We also hypothesize that gains will be maintained at 3-month follow-ups. Third, changes in overall health levels will demonstrate the cost-effectiveness of iABCT. Fourth, significant associations will be found between changes in compassion, self-compassion, dispositional mindfulness, general health, purpose in life, nonattachment, attachment styles, self-criticism, positive and negative affects, and happiness. Specifically, improvements in happiness scores and overall health status will be predicted by self-reported self-compassion. Increments in secure attachment style would mediate the relationship between self-compassion and happiness. Finally, low rates of adverse or unwanted effects are expected.

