### Outcome Measures

Participants will be assessed at baseline (preintervention), postintervention, and 3-month follow-up after they complete the intervention. Assessments will be conducted online via the website [36], where the iABCT will be hosted, and via a telephone interview at pre- and postintervention, except for the 3-month follow-up that will be conducted only via the website. Both participants and researchers will receive email reminders of each assessment time. The study variables and assessment times are summarized in Table 2.

**Table 2 table2:** Study measures, time of assessment, and source of measurement.

Measures	Aim	Assessment point	Assessment source
Admission interview	Screen eligibility criteria (inclusion/exclusion)	Pre^a^	Phone interview
Sociodemographic data	Sex, age, educational level, occupation, and civil status	Pre	Phone interview
M.I.N.I. 7.0.2.^b^	Psychological diagnosis (exclusion criterion)	Pre	Phone interview
Meditation data	Source of learning, frequency, duration of each session (in minutes), lifetime practice (in years), and context of practice	Pre	Phone interview
PHI^c^	Well-being	Pre, post^d^, and FW^e^	Web
SCS-26^f^	Self-compassion	Pre, post, and FW	Web
Compassion scale	Compassion	Pre, post, and FW	Web
FSCRS-SF^g^	Two forms of self-criticism: inadequate self and hated self and the ability to self-reassure	Pre, post, and FW	Web
FFMQ-15^h^	Dispositional mindfulness and mindfulness facets	Pre, post, and FW	Web
RQ^i^	Attachment styles	Pre, post, and FW	Web
GHQ-12^j^	Mental health recent symptoms, feelings, or behaviors	Pre, post, and FW	Web
NAS-7^k^	Nonattachment	Pre, post, and FW	Web
I-PANAS-10-SF^l^	Positive and negative affects	Pre, between modules, post, and FW	Web
PIL-10^m^	General sense of meaning and purpose in life	Pre, post, and FW	Web
Compassion Practice Quality Questionnaire	Difficulties related to the practice of compassion meditation	Between modules, post, and FW	Web
Expectations and Satisfaction Questionnaires	Participants’ expectations before the intervention and their satisfaction after it	Pre and post	Web
UAQ^n^	Usability and acceptability of the internet-based intervention	Post	Web
Qualitative opinion interview	Opinions on the internet intervention, the modules, and unwanted or unexpected effects	Post	Phone call
Attrition rate	Percentage of participants that drop out of the intervention after accessing it for the first time	Post	Web

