### Feasibility Outcomes

Feasibility outcomes will assess the implementation of iABCT regarding adherence (ie, attrition rate), patterns of use for each participant (eg, length of the intervention, time spent each in each module, how many times they enter the modules), participants’ acceptability (*Expectations and Satisfaction Questionnaires* adapted from Borkovec and Nau [39]), usability (*The Usability and Acceptability Questionnaire* [40,41]), and opinion (qualitative interview).

The *qualitative opinion interview* has been specifically developed to assess participant opinions on the web-based intervention. This semistructured telephone interview includes 14 questions with both quantitative and qualitative open questions: 7 of which refer to the usefulness of the intervention, components, modules, information provided, and multimedia elements (eg, images, audios, videos, PDF files) rated on a scale of 1 to 5 (1=not at all; 2=not very; 3=somewhat; 4=very; 5=extremely) and 2 dichotomous questions (“yes” or “no”) regarding whether they would consider it useful to have the program at their disposal for additional time after completion of the treatment, as well as whether they would like to have longer access. Additionally, interviewers would request to expand on the participants’ qualitative responses for each question. Finally, 2 open questions will be included to assess adverse or unwanted effects and facilitators and barriers to the intervention received.

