A data monitoring committee (DMC) will be set up, comprising a psychiatrist, the principal investigator, and an independent clinical psychologist familiarized with the administration of internet-based interventions. The DMC will meet 3 times throughout the trial—after the baseline, posttreatment, and at follow-up measurements—but will be available on request at any time to provide support and information to all parties where necessary. The DMC will function independently of the sponsors and funders and will oversee and safeguard all trial participant interests, monitoring the overall conduct of the trial and ensuring the safety of participants by systematically checking negative events and reacting to any extreme distress or risk. In the case of an adverse event emergency, participants will be contacted and encouraged to receive additional help and counseling. Interim analyses are not contemplated in this study, although the DMC could request them if considered necessary for proper conducting of the trial and/or participant safety. Important protocol modifications will be communicated to relevant parties (ie, trial participants, trial registries, journals, ethical committee, and researchers). Results will be disseminated to relevant health care and professional communities and the general population via social media, in peer-reviewed and popular science journals, and at scientific and clinical conferences. Authors of the works derived from this study will be the investigators collaborating in this clinical trial, and there is no intention of using professional writers. A professional native English-speaking editor will check the language and grammar of English written content. Data generated in this trial (ie, full protocol, participant-level data set, and statistical code) will be made available upon reasonable request to the corresponding author.

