### Statistical Analysis Plan

Normality and homoscedasticity data assumptions will be checked using Kolmogorov-Smirnov (K-S) and Levene tests. Significant differences on categorical variables (eg, sex, educational level, occupation, etc) will be assessed using a chi-square test. Attrition and dropout rates will be calculated by reporting percentages and patterns of missing data. The Little missing completely at random (MCAR) test will be used to assess the assumption that data are MCAR [55]. Means and SDs will be reported for all the measures at each assessment point. A preliminary efficacy analysis will be performed using means of comparison for related samples based on intention-to-treat and per-protocol analyses. Mixed model analyses for primary and secondary outcome measures will be implemented using the linear mixed-effects models (MIXED) procedure with 1 random intercept per subject. *Time* will be treated as a within-group factor, and significant effects will be followed up with pairwise comparisons (adjusted by a Bonferroni correction). Sensitivity analyses will be performed to assess the robustness of the findings in terms of different methods for handling missing data (ie, mixed models with and without imputation, maximum-likelihood estimation, and maximum-likelihood multiple imputation) [56]. Within-group effect sizes (pre vs post and pre vs 3-month follow-up) will be reported using Cohen *d* and its 95% CI. For the analyses of associations between the intervention outcomes, predictors of change, and mechanisms of actions, several statistical tests will be performed such as Pearson correlation, multiple regressions, and mediation analysis using the bootstrapping approach [57]. A cost-effectiveness and cost-utility analysis will be conducted using the GHQ-12 based on literature proposals [58,59]. The mapping technique proposed by Lindkvist and Feldman [59] will be used to predict health state utility values using a crosswalk transformation algorithm from the GHQ-12 to the health utility measure (EuroQoL–5 dimension [EQ-5D]). Spanish tariffs of EQ-5D will be used as the reference population [58,60]. Additionally, participants’ qualitative responses regarding adverse or unwanted effects and facilitators and barriers to the intervention received will be explored using a qualitative content analysis and coding and the categorizing data approach by counting the frequency of words with NVivo software (QSR International). Statistical analyses of quantitative data will be performed using SPSS version 23 for Windows (IBM Corp). The statistical analysis plan (SAP) will be revised by all the study team members before the database is locked for use in the final statistical analysis. Any discrepancies or changes made between the analysis plan in this protocol and final SAP will be explained and reported.

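### The plan hypothesises low rates of unwanted effects, but asks about them explicitly only in one end-of-intervention interview and quantifies the answers only by word frequency

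*Protocol article*

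**What the plan says.** **Aim and hypothesis.** In Aims and Hypotheses, the fifth objective is "to assess adverse or unwanted effects and facilitators and barriers to the intervention received", and the last hypothesis is that "low rates of adverse or unwanted effects are expected". No threshold, numerator or denominator is given.

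**Collection.** Under Feasibility Outcomes, the qualitative opinion interview is described as a semistructured telephone interview in which "2 open questions will be included to assess adverse or unwanted effects and facilitators and barriers to the intervention received". Table 2 schedules it at the post assessment only. Outcome Measures says that assessments use the website and a telephone interview, "except for the 3-month follow-up that will be conducted only via the website".

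**Analysis.** The Statistical Analysis Plan section sends these answers to qualitative content analysis and coding and to "the categorizing data approach by counting the frequency of words with NVivo software". The same section specifies percentages for attrition and dropout, but none for unwanted effects.

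**Oversight.** Ethics and Dissemination has a data monitoring committee (DMC) that meets after the baseline, post-treatment and follow-up measurements and protects participants by "systematically checking negative events and reacting to any extreme distress or risk". It does not say which data these checks use.

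**The concern.** A rate of unwanted effects is a number of affected participants divided by a number of participants asked or exposed. The one quantification named counts words. It can rise because one person speaks at length, and on its own it does not separate a report of an effect from a denial of it.

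Timing is the second part. The programme is self-applied, without systematic telephone support, over an estimated 8 weeks and at most 10. One open question at the end relies on recall. It can miss effects that came and went, effects in people who left and are not interviewed, and effects that appear by 3 months.

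At stake are the answer to a stated objective, and participant-level harm data for the randomised trial that this study is meant to prepare. A later analysis plan can change how answers are counted, but it cannot recover events that nobody was asked about.

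**Working it through.** The article states no rate, threshold or precision target for unwanted effects, so there is no figure to reproduce. The check compares the passages and then shows what a participant-level analysis would give.

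**1. Does the stated quantification give a rate?** Two mentions of a word could come from two affected participants (2/35 = 5.7%), from one affected participant (1/35 = 2.9%), or from two denials (0/35 = 0%). The word count is 2 each time. The coding named in the same sentence could separate these cases, but no count of participants per code is stated.

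**2. When are unwanted effects explicitly asked about?**

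| Period | What Table 2 schedules | Named as an unwanted-effects measure? |
|---|---|---|
| Between modules | Compassion Practice Quality Questionnaire; I-PANAS-10-SF; patterns of use | No |
| Post | Qualitative opinion interview; the scales, including GHQ-12 | Yes, the interview only |
| 3-month follow-up (web only) | The scales, including GHQ-12, I-PANAS-10-SF and the practice questionnaire | No |

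For people who withdraw, the Recruitment section plans an attempt at contact to obtain reasons and feasibility data. Unwanted effects are not mentioned there.

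**3. What would a participant-level proportion deliver?** Inputs: the minimum sample of 35 (Sample Size); 11.6% dropout, quoted in the Introduction from a cited web-based trial; and, as an assumption, 30% not interviewed. The article gives no dropout assumption of its own. Interviewed: 35 × 0.884 = 30.9, so 31; 35 × 0.70 = 24.5, taken as 24.

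For zero reports, the exact two-sided 95% upper limit is 1 − 0.025^(1/n). For two reports, the limits are Clopper-Pearson.

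| Interviewed | 0 reports: 95% CI | 2 reports: proportion (95% CI) |
|---|---|---|
| 35 | 0 to 10.0% | 5.7% (0.7 to 19.2%) |
| 31 | 0 to 11.2% | 6.5% (0.8 to 21.4%) |
| 24 | 0 to 14.2% | 8.3% (1.0 to 27.0%) |

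**4. What do missing interviews add?** Suppose two effects are reported. Among all 35 starters, the proportion lies between 2/35 (nobody missed is affected) and (2 + number missed)/35 (everybody missed is affected):
- 4 missed: 5.7% to 6/35 = 17.1%.
- 11 missed: 5.7% to 13/35 = 37.1%.

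Steps 3 and 4 show the precision of the repaired analysis. The intervals in step 3 follow from the sample size and would be the same under any sound method, so they do not measure the harm done by counting words.

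**The case against.** The strongest reply has four parts.

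- **Word counting is not the whole method.** This stands. Content analysis and coding are named in the same sentence, and coded answers could be turned into participants per category. A reader might infer that the hypothesis is untestable. The article does not support that: it shows only that the stated analysis does not produce the quantity, and a final analysis plan, which the article mentions and which is not shown, could add the count.
- **Distress is measured elsewhere.** This stands in part. Negative affect and practice difficulties are recorded between modules and at follow-up, GHQ-12 is recorded at post and follow-up, withdrawals are to be contacted, and the DMC is available at any time. The Discussion says that difficulties and unwanted effects will be directly asked about. Yet none of these measures is designated as recording unwanted effects or as feeding the DMC.
- **The study is small and its main aim is feasibility.** This stands and limits the severity. The participants are healthy adults, and no decision rule depends on the low-rates hypothesis.
- **The DMC's independence is not contradicted.** This stands. A reader might infer a contradiction because the committee is described as "comprising a psychiatrist, the principal investigator, and an independent clinical psychologist". But the claim made is "The DMC will function independently of the sponsors and funders", which does not extend to the investigators, and nothing in the article makes the principal investigator the sponsor. That point is not part of this finding.

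**Conclusion.** The concern holds and is of moderate severity. Followed as written, the plan yields themes and word frequencies from one post-intervention interview. It does not yield the rate in its own hypothesis. It does not explicitly ask about unwanted effects during the modules or at 3 months, and it does not ensure that people who leave are asked. It gives the DMC's checks no named data source.

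The direction of any error cannot be fixed from the article. Under-recording is plausible if effects are transient or lead people to leave, but that is an assumption, and the article has no event rates from which to size it. What can be sized is the uncertainty left once participants are counted. With no reports, the upper 95% limit runs from 10.0% (35 interviewed) to 14.2% (24 interviewed, assuming 30% are missed). With two reports, missing interviews alone would allow up to 17.1% (4 missed) or 37.1% (11 missed) among the 35 starters. A finding of low rates would need that qualification even after repair.

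**What to change.** **Analysis.** Define the measure as the number and percentage of participants with at least one coded unwanted effect. Report it over those asked and over all who accessed the programme, each with an exact 95% confidence interval. State how many were never asked, and label the second figure a minimum, since it treats them as unaffected. Use content analysis and word frequency for description only.

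**Collection.** Add one fixed yes/no unwanted-effect item with free text to the existing between-module, post and 3-month web assessments.

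**Oversight.** Name these entries, with the interview reports, as the data source for the DMC's checks of negative events.

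**Cost.** The analysis change is a matter of wording before database lock and uses interviews already planned. The web item adds slight participant burden and a small change to the platform. The article reports that enrolment began in February 2020, so the item would need a minor amendment, and participants already under way would have no answers for earlier modules. Report the number covered at each time point.

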
## Results

Enrollment started in February 2020 and will be finished in April 2020. Data analysis will start in October 2020.

## Discussion

There is incipient evidence that supports the feasibility, acceptance, and preliminary effectiveness of CBIs delivered over the internet. However, to our knowledge, the existing research has mostly been conducted in English-speaking countries.

This paper describes the study protocol to investigate the feasibility of iABCT, a web-based version of the ABCT adapted to be completely self-applied over the internet for the general population. Results from this study will, for the first time, show data regarding the feasibility, acceptability, and preliminary evidence of web-based compassion (and self-compassion) training—that is, the adapted iABCT—in Spanish-speaking countries on a sample of healthy people. Moreover, further aspects of their implementation (ie, facilitators and barriers) and mechanisms of change will be investigated.

ABCT, in a face-to-face group format, has shown its efficacy and applicability for healthy people and for patients with fibromyalgia. This intervention focuses on training compassion and self-compassion to build a secure individual attachment style, which has been considered key for therapeutic efficacy [6,61]. It is expected that those improvements in compassion, self-compassion, and secure attachment will also promote an increased sense of well-being. In this study, specific measures of well-being and mental health (ie, happiness, overall health status, purpose in life, and positive and negative affects) have been included. Findings from this study will be congruent with the growing research supporting the benefits of using the internet to deliver evidence-based interventions [62-64] and will add valuable data to the incipient research field on the potential of self-applied CBIs via the internet [8,25,26,65].

We would like to highlight the relevance of conducting a feasibility study before designing a larger RCT due to the novelty of cultivating compassion via the internet (ie, CBIs). Moreover, despite the wide use of meditation-based interventions (eg, MBIs and yoga-based programs) over the last decade, compassion in the sense with which it is used here—the feeling that arises in witnessing another’s suffering and that motivates a subsequent desire to help [66]—is a relatively new concept for the general population in Spanish-speaking countries, where it is traditionally associated with a “feeling of commiseration and pity for those who suffer hardship or misfortune” [67]. However, the entry for this term in the official Spanish language dictionary of the Royal Spanish Academy has recently had its definition updated to a “feeling of pity, tenderness, and identification toward others’ afflictions” [68], which is closer to the psychological definition and the evolutionary perspective of compassion [66] and may reflect the assimilation of and re-conceptualization of the term.

This trial has been designed to cover the 8 areas of feasibility as suggested by Bowen et al [69]: *acceptability* (ie, how the intended individual recipients react to the intervention); *demand for the intervention* (ie, assessed by gathering data on estimated use or by actually documenting the use of a selected intervention); *implementation* (ie, the extent, likelihood, and manner in which an intervention can be fully implemented as planned and proposed, often in an uncontrolled design); *practicality* (ie, the extent to which an intervention can be delivered when resources, time, commitment, or some combination thereof is constrained in some way); *adaptation* (ie, to assess the necessity of changing program contents or procedures to be appropriate in a new situation); *integration* (ie, to assess the level of system change needed to integrate a new program or process into an existing infrastructure or program, as in our case using the website of Psychology and Technology); *expansion* (ie, to examine the potential success of an already-successful intervention with a different population or in a different setting, such as the original ABCT); *limited-efficacy testing* (ie, to test an intervention in a limited way, such as using a convenience sample, with shorter follow-up periods or with limited statistical power). In addition, this research will use a combination of methods (ie, qualitative and quantitative approaches) that best suit its feasibility study design based on author recommendations [70]. Key aspects of possible barriers to its implementation (ie, difficulties and unwanted or unexpected effects of the compassion meditation practice) will be directly asked and investigated.

Finally, based on recent literature findings, several constructs that have been associated with the promotion of well-being will be assessed together with compassion and self-compassion outcomes (eg, mindfulness, self-criticism, attachment styles, nonattachment, or purpose in life) [1,10,45,47,71-73]. Specifically, we would highlight the role of self-criticism (inadequate self and hated self and the ability to self-reassure), which is linked to various forms of psychological disorders [45,74]. Findings from this study would also provide preliminary data on associations between these variables.

